### **Assessment tools/outcome measures**

The patients will be asked throughout the project to fill out questionnaires about their health and overall condition. The survey focuses on both mental, physical and social conditions.

#### *Primary outcome measure*

The primary outcome measure of this trial will be one of eight subdimensions, physical function, measured by "SF-36" which is a 36-item questionnaire that produces scales for both mental and physical health (19,20). The questionnaire has been used previously and is well validated in similar studies (21), is sensitive to treatment change (22) and is a sufficient measure of functional status (23).

Other outcome measures will be "Fatigue" measured by Chalder Fatigue Scale (score 0-3 with 11 items, max score/fatigue = 33 points) (24) and mental function in SF36 (0-100) (20). Outcome success criteria will be > 10 points improvement in physical function in SF36 analyzed by a 0-100 scale, where 100 is best and 0 is worst (13), 50% recovery or a score of 75 points (25).

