## **Design, methods and analysis**

### ***Inclusion and exclusion:***

Patients who meet the diagnostic criteria CFS / ME according to the Fukuda CDC 1994 criteria (1) will be offered inclusion in our treatment study and receive outpatient, individual treatment. Exclusion: Absence of fatigue. Age <18 years and > 62 years. Severe somatic or psychiatric disorder. Pregnancy. Problematic drug use. Poor skills in Norwegian language.

***Design:*** A randomised controlled trial is a suitable design to answer our primary research questions on whether CBT has an effect in CFS/ME. The trial is not blinded for intervention, but the investigator is blinded to measurement of the outcome variables. All the groups will be treated equal during the trial, except from exposure to the interventions that are to be evaluated.

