#### *Analyses:*

Calculation of sample size and power. We have calculated sample size assuming a mean change in SF-36 score of 10, 5, and 0 from baseline of respectively short I-CBT, standard CBT, and WLC group, a ‘within cell’ standard deviation (SD) on 15 and a correlation between baseline and post score on 0.3 (r-squared on 0.1). For a two-sided test with 5 % significance level and 80 % power, we calculated that we needed 40 patients in each group, 120 in total. Assuming a maximum drop-out level of 25 %, we calculated that we needed an additional number of 18 patients in each group, 174 patients in total. A mean change in SF-36 score of 10, 10, and 0 for short, standard, and WLC groups would increase power to 90 %.

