### Statistical analyses:

ANCOVA and "mixed random effects regression" will be used to compare the post-score / outcome variables in the three intervention cohorts (among others physical function in SF36). All analyzes will be adjusted for baseline scores with postscore as outcome variables. The three intervention cohorts will be compared at X, Y and Z months. We will perform separate analyzes for each follow-up time (ANCOVA) as well as combined analyzes for all times (mixed random effects regression). The results will be presented as "least-squares means with standard errors (SE). Differences between cohorts will be reported with 95% confidence interval (CI).

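### The 75-point success criterion requires no improvement, so a patient who starts at 75 or above can count as a success unchanged or worse; "50% recovery" is undefined

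*Protocol*

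**What the plan says.** The protocol, under Primary outcome measure, states: "Outcome success criteria will be > 10 points improvement in physical function in SF36 analyzed by a 0-100 scale", with the scale running so that higher is better ("where 100 is best and 0 is worst"). The same sentence then adds "50% recovery or a score of 75 points". It does not say what the 50% is a percentage of, whether 75 means at least 75, whether a patient must start below 75, or whether the list is one rule or several definitions.

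Under Inclusion and exclusion, entry is by diagnosis: "Patients who meet the diagnostic criteria CFS / ME according to the Fukuda CDC 1994 criteria (1) will be offered inclusion". The exclusions begin "Exclusion: Absence of fatigue. Age <18 years and > 62 years. Severe somatic or psychiatric disorder" and go on to pregnancy, drug use and language. None refers to a physical function score, high or low.

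The planned comparison is on the continuous score. Under Statistical analyses: "All analyzes will be adjusted for baseline scores with postscore as outcome variables". The sample size, under Analyses, is likewise based on mean change. No analysis of a success proportion is described.

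**The concern.** The three criteria are of different kinds: an absolute change, a percentage and an absolute level. A level can describe where a patient ends up, but it says nothing about improvement unless the starting point is restricted. Here it is not, so the label of success can go to someone who has not changed or has worsened. The undefined percentage adds a second possible gap at the low end of the scale.

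What is at stake is the meaning of any success rate the trial reports. The protocol says in its background that an evaluation of CBT can inform patients and their next of kin, and that a few studies report harm or no effect. In that setting a success count that can include patients who declined would mislead. The open wording also leaves room to settle the definition after the data are seen, in a trial that is not blinded to intervention.

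**Working it through.** **1. What the plan's own figures rest on.** The protocol gives no success rate to reproduce. It does give a sample size: mean changes 10, 5 and 0, SD 15, r-squared 0.1, 40 per group, 80% power. For a three-group ANCOVA F test the noncentrality is n × Σ(mᵢ − m̄)² / [SD² × (1 − R²)] = 40 × (25 + 0 + 25) / (225 × 0.9) = 2000 / 202.5 = 9.88, which gives 79.95% power. With changes 10, 10 and 0, power is 90.4%, against 90% stated. Both reproduce without any success criterion, so the sample size does not depend on the rule.

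**2. Smallest change that counts as success, by baseline b.** The criteria are: change > 10; change ≥ 0.5b (50% of baseline) or change ≥ 0.5(100 − b) (half the gap to 100); and change ≥ 75 − b (75 read as at least 75). Joined by 'or', the easiest one decides.

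| Baseline | Needed if 50% is of baseline | Needed if 50% is of the gap to 100 |
|---|---|---|
| 0 | 0 (degenerate) | more than +10 |
| 10 | +5 | more than +10 |
| 20 | +10 | more than +10 |
| 25 to 60 | more than +10 | more than +10 |
| 65 | +10 | +10 |
| 70 | +5 | +5 |
| 75 | 0 | 0 |
| 80 | −5 allowed | −5 allowed |
| 85 | −10 allowed | −10 allowed |
| 90 | −15 allowed | −15 allowed |

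From 65 upward the two readings agree, because the 75-point criterion decides. The low-baseline gap exists only if the percentage is of baseline. A decline is never a success from a low baseline.

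**3. How often this could occur.** The documents give no baseline mean, so this is an illustration. Assumptions: no treatment effect, normal scores with SD 15 (the protocol's value), correlation 0.3 (the protocol's value) to 0.7, baseline mean 40 to 60, scores rounded to 5-point steps and limited to 0–100, and 50% taken of baseline.

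| Quantity | Range |
|---|---|
| Start at 75 or above | 1.5–20% |
| Success by more than 10 points alone | 14–24% |
| Success by any of the three | 18–33% |
| Success with no gain or a decline (share of all patients) | 0.1–7% |
| Success with an actual decline (share of all patients) | 0–4% |

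The 7% and 4% occur at mean 60 with correlation 0.7. At the protocol's correlation of 0.3, decliners counted as successes are at most 2.5%, and about 0.4% or less at means of 40 to 50. Taking 50% as half the gap leaves the upper figures essentially unchanged.

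**4. Does the rule shrink the difference between arms?** Same set-up, with a mean change of 10 in one arm and 0 in the other. Difference in success proportion:

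| Baseline mean | Correlation | More than 10 alone | Any of three |
|---|---|---|---|
| 40 | 0.3 | 0.202 | 0.200 |
| 40 | 0.7 | 0.274 | 0.276 |
| 50 | 0.3 | 0.204 | 0.224 |
| 50 | 0.7 | 0.273 | 0.301 |
| 60 | 0.3 | 0.203 | 0.255 |
| 60 | 0.7 | 0.271 | 0.320 |

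The absolute difference is about the same or larger under the joined rule.

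**The case against.** The strongest reply is that nothing confirmatory depends on the rule. The hypotheses, the sample size and the ANCOVA and mixed model all use the score itself, where a fall from 85 to 75 counts as a fall. No responder analysis is described, and detailed coding is often left to a SAP, which is not at hand. This stands as a limit on the consequence. It does not remove the defect: the protocol does not defer the definition but states one, and the one it states misclassifies.

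A second reply is that the plural 'criteria', with separate citations, may mean separate benchmarks. That is possible, but the 75-point benchmark then has the same fault on its own.

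A third is that patients with a disabling condition rarely start at 75 or above. That is plausible, and at an assumed mean of 40 with SD 15 the share of successes without gain is below 1%. But the entry criteria do not exclude such patients, and no baseline distribution is given.

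Two stronger readings are not supported. A reader might infer that the rule also rewards trivial gains near zero. That holds only if 50% is taken of the baseline score, which the text does not say; the firm point is that the term is undefined. A reader might also infer that the looser rule dilutes the treatment contrast. Over the range examined, the absolute difference between arms does not shrink.

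**Conclusion.** The point holds in a limited form. As written, the 75-point criterion labels a patient who starts at 75 or above a success with no change, and one who starts above 75 a success even after a decline. This follows from the text alone, under either reading of the percentage and whether the criteria are joined or separate. The percentage criterion needs a formula before it can be applied.

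The size depends on an unknown baseline distribution. Under the assumptions shown, the joined rule raises the success rate from 14–24% to 18–33%. Successes without gain range from negligible to about 7% of all patients, and successes with a decline reach at most about 4%. The baseline-adjusted comparison and the sample size are unaffected. This should be corrected before any success rate is reported, but it does not threaten the main result.

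**What to change.** - Use the protocol's first criterion, a gain of more than 10 points in SF-36 physical function from baseline, as the single responder definition.
- Report reaching 75 as a separate row, counted only for patients who were below 75 at baseline and also gained more than 10 points. State that 75 means 75 or more.
- State the formula for the 50% criterion, including its reference value and how a baseline of 0 is handled, and report it only descriptively.

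The cost is a change of wording and a few lines of analysis code, using scores already collected. The reported success rates will be lower.

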**Figure 2: Examples of outcome for physical function and fatigue (n = 3):**

[figure not shown]

For both figures from top to bottom: Standard CBT, Short I-CBT and Control group (WLC).

[figure not shown]

#### *Secondary outcomes:*

Physical condition VO2 max (26), pain (NRS), tender points, negative affect (HADS), an “amount” of subjective health complaints (SCL-90, SHC) (27,28). We will be able to combine these above-mentioned outcomes, for example, changes in “fatigue” with changes in specific cognitions and behaviour responses as moderators. In addition, there will be baseline targets, including neuropsychological parameters, relaxation capacity (GFM-52) (29) and psychometric measures as predictors of the main outcome measurements.

#### *Analyses:*

Calculation of sample size and power. We have calculated sample size assuming a mean change in SF-36 score of 10, 5, and 0 from baseline of respectively short I-CBT, standard CBT, and WLC group, a ‘within cell’ standard deviation (SD) on 15 and a correlation between baseline and post score on 0.3 (r-squared on 0.1). For a two-sided test with 5 % significance level and 80 % power, we calculated that we needed 40 patients in each group, 120 in total. Assuming a maximum drop-out level of 25 %, we calculated that we needed an additional number of 18 patients in each group, 174 patients in total. A mean change in SF-36 score of 10, 10, and 0 for short, standard, and WLC groups would increase power to 90 %.

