The Department for Pain and Complex Symptom Disorders (ASSL), CFS/ME outpatient clinic, St. Olav’s Hospital, has since 2008 received patients with fatigue for inclusion in a consecutive, randomised, controlled treatment trial with short and long/standard individual cognitive behavioural therapy as intervention. Thus, we will use the collected data from ASSL, and plan to have enough patients included per 01.01.2012 according to conducted power calculation. The study protocol is approved by the Regional Ethics Comity (REK), project number 4.2008.2586, and is also registered in Clinical trials.gov. The trial is also referred to in a report from the Norwegian Research Centre for Health Services (5). The Norwegian Directorate of Health has referred to this report in a letter to the Department for Health and Care which has requested more documentation on treatment for chronic fatigue syndrome, CFS/ME. Our project has started without research funding as an outpatient offer to this group of patients. The collection of data will soon be completed, and everything is now ready for a PhD candidate to start working on the material.

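### The drop-out allowance does not follow from its inputs: 25% loss on 40 per group needs 54 per group (162 in total), while the stated 58 (174) allows for 31% loss

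*Protocol*

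**What the plan says.** The sample-size paragraph of the Protocol, under Analyses, proceeds in three steps.

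- **Inputs.** It works by "assuming a mean change in SF-36 score of 10, 5, and 0 from baseline" for short I-CBT, standard CBT and the waiting list respectively, with "a ‘within cell’ standard deviation (SD) on 15" and a baseline-to-post correlation of 0.3, given as an r-squared of 0.1.
- **Evaluable number.** "For a two-sided test with 5 % significance level and 80 % power", it concludes that "we needed 40 patients in each group, 120 in total".
- **Drop-out.** "Assuming a maximum drop-out level of 25 %, we calculated that we needed an additional number of 18 patients in each group". The total is then given as 174.

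The same paragraph adds that changes of 10, 10 and 0 would raise the power to 90%. It gives no other drop-out rate, no safety margin and no other reason for extra patients.

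The Protocol's background section relies on this calculation for the timing of inclusion: the investigators "plan to have enough patients included per 01.01.2012 according to conducted power calculation". That section repeats none of the numbers.

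**The concern.** Three linked figures are given: 40 evaluable per group, 25% loss, 58 recruited per group. Any two determine the third, and these three are not compatible. One of the following must be true:

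- the allowance is really about 31%;
- the evaluable number behind the calculation was not 40;
- the inflation was miscalculated.

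The Protocol does not let the reader tell which. This is the only recruitment target in the document, and the background section uses the calculation to judge when enough patients have been included. Anyone who repeats the calculation for the trial report will get 162, not 174. Depending on the explanation, the trial randomises 12 more patients than its assumptions require, allows for more loss than it states, or has more power than it states.

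**Working it through.** **Inputs** (all from the sample-size paragraph): mean changes 10, 5, 0; SD 15; r-squared 0.1; two-sided 5%; three equal groups; 40 evaluable per group; drop-out at most 25%; 18 extra per group; 174 in total.

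**Step 1: does the 40 reproduce?** The Protocol does not name the test. I used the overall three-group ANCOVA F-test with one covariate.

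- Residual SD = 15 × √(1 − 0.1) = 14.23, so the residual variance is 202.5.
- Noncentrality = n × Σ(mean − grand mean)² / variance = 40 × (25 + 0 + 25) / 202.5 = 9.88.
- Degrees of freedom: 2 and 3 × 40 − 3 − 1 = 116.

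| Scenario | Power at 40 per group | Stated |
|---|---|---|
| 10, 5, 0 | 0.7995 | 80% |
| 10, 10, 0 | 0.904 | 90% |

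Both stated powers come out at 40 per group. With r-squared taken as 0.3² = 0.09 they are 0.795 and 0.901. The evaluable number is therefore sound, and the mismatch arises after it.

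**Step 2: does the 58 reproduce?** To keep n after a proportion d is lost, recruit n/(1 − d).

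| Method | Per group | Total |
|---|---|---|
| 40/(1 − 0.25) = 53.3, rounded up | 54 (+14) | 162 |
| 120/(1 − 0.25), on the total | – | 160 |
| Shortcut 40 × 1.25 | 50 (+10) | 150 |
| 40 × 1.25² | 62.5 | – |
| 40 × 1.25/0.75 | 66.7 | – |
| 40/0.75² | 71.1 | – |
| **Protocol** | **58 (+18)** | **174** |

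None gives 58. Since 3 × 58 = 174, the extra 18 and the total agree with each other, so a slip in the total alone does not explain it.

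**Step 3: what does 58 correspond to?**

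- Loss that takes 58 down to 40: 18/58 = 31.0%.
- Evaluable number left from 58 at 25% loss: 58 × 0.75 = 43.5 per group.
- Evaluable number that would lead to 58 at 25%: 43/0.75 = 57.3, rounded up to 58. The Protocol says 40, and its inputs support 40.

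**Step 4: power at 25% loss from 174.** With the same F-test and changes of 10, 5, 0:

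| Evaluable per group | r-squared 0.09 | r-squared 0.1 |
|---|---|---|
| 43 | 0.825 | 0.830 |
| 44 | 0.835 | 0.839 |

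That is about 83%.

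**Step 5: size of the gap.** 174 − 162 = 12 patients, 4 per group, or 12/174 = 7%.

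**The case against.** The arithmetic is hard to dispute; the case on the other side is about weight and wording.

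- **The error is conservative.** This stands. At the stated 25% loss the trial keeps more than its planned power, and no test, estimate or conclusion changes. That limits the seriousness, but a target that contradicts its own inputs still needs correcting.
- **A margin may have been intended.** Inflating by 1/(1 − d) secures 40 completers only on average. If each patient drops out independently with probability 0.25, the chance of at least 40 completers in a group is 0.63 with 54 recruited and 0.89 with 58. A margin for this would be reasonable, but the Protocol states none and presents the 18 as what a loss of at most 25% requires.
- **The stated power is not itself wrong.** This also stands. The 80% is attached to 120 evaluable patients, and there it reproduces. It fails to match only when read together with 174 recruited and 25% loss.
- **Fewer patients may no longer be possible.** The Protocol's summary says inclusion is nearly complete, and it states no formal rule for ending recruitment. A saving of 12 patients may therefore be theoretical, which favours the correction that keeps 174.
- **The overall F-test is a reconstruction.** The Protocol speaks only of a two-sided test. The reconstruction reproduces both stated powers, and the drop-out arithmetic does not depend on it.

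**Conclusion.** The concern holds. From 40 evaluable per group and 25% drop-out, the recruitment target is 54 per group and 162 in total. The stated 58 and 174 correspond to 31% drop-out. The discrepancy is 12 patients (7% of 174) and is in the safe direction: at 25% loss, power is about 83% rather than 80%.

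The 54 and the 31% rest only on the Protocol's own figures and simple division. The 83% also assumes the overall three-group ANCOVA F-test with the stated SD and r-squared. The document does not show which of the three figures was the mistaken one. What is certain is that they cannot all be right. The point should be corrected, but it does not threaten the trial's conclusions.

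**What to change.** Restate the sentence so that the evaluable number, the drop-out rate and the recruitment target agree. Either of these does so:

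1. With a maximum drop-out of 25%, 54 patients per group and 162 in total are needed to retain 40 per group and 80% power for the overall three-group comparison.
2. Keep 174 and say that 58 per group leaves about 43 per group at 25% drop-out (about 83% power for that comparison) and 40 per group at 31% drop-out (80% power).

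With inclusion close to complete, the second is the easier choice, since it changes nothing in the conduct of the trial. If the extra patients were a deliberate margin, say so and give the reason. If the test behind the original calculation was not the overall F-test, name the one that was used in place of that wording.

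The cost is one sentence. No further patients are needed; the first option would need 12 fewer, if recruitment still allows it.

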### Statistical analyses:

ANCOVA and "mixed random effects regression" will be used to compare the post-score / outcome variables in the three intervention cohorts (among others physical function in SF36). All analyzes will be adjusted for baseline scores with postscore as outcome variables. The three intervention cohorts will be compared at X, Y and Z months. We will perform separate analyzes for each follow-up time (ANCOVA) as well as combined analyzes for all times (mixed random effects regression). The results will be presented as "least-squares means with standard errors (SE). Differences between cohorts will be reported with 95% confidence interval (CI).

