## Is cognitive behavioural therapy a good treatment for chronic fatigue syndrome?

### Summary:

The Norwegian Directorate of Health has requested documentation on treatment for chronic fatigue syndrome, CFS/ME. With this trial, The National Competence Centre for Complex Symptom Disorders (NKSL) wants to contribute to knowledge on whether cognitive behavioural therapy is good treatment for CFS/ME. Even though standard, individual CBT together with graded exercise therapy so far is the best documented treatment, there is no national or international consensus due to few randomised trials, varying quality and moderate evidence. Therefore, our goal is to test the effect of individual standard CBT, in a randomized, controlled 1-year follow-up trial. Our second goal will be to test the effect of a newly developed and shorter individual CBT (I-CBT). If the shorter therapy turns out to be as good as or better than standard CBT, the shorter therapy will be an equal and more cost-effective treatment. Patients with nonspecific fatigue will undergo a thorough, multidisciplinary assessment at the The Department for Pain and Complex Symptom Disorders (ASSL), St. Olav`s Hospital, to be diagnosed with CFS/ME or other fatigue conditions. Patients diagnosed with CFS/ME will be offered treatment in our trial with randomisation to either short I-CBT or standard individual cognitive behavioural therapy or a control group. Primary outcome measures are physical function, health related quality of life and fatigue. NKSL is a research group at ASSL, St. Olav`s Hospital that wants research to be the basis for the operation of its three outpatient clinics; the clinic for pain, the clinic for CFS/ME and the clinic for assessment to work related rehabilitation at Hysnes, Norway.

In our opinion, this study fits perfectly with the announcement:

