**Standardised CBT, long intervention:** The intervention consists of 16 weekly sessions plus a booster session four weeks after the 16th session, ad modum "Chalder/Kings College". The actual therapy manual is based on previous manuals from similar trials and associated with the fear avoidance theory (FA) of CFS. The FA theory focuses on the link between cognitive and behavioural responses. The following main elements are included in the intervention: (a) information and explanation of the CFS symptoms based on contemporary knowledge on both physical and psychological components, (b) agreement on goals for the

treatment (c) reading of self-help guides like *Coping with Chronic Fatigue* (d) avoidance of excessive activity or rest and/or sudden change in activity, (e) planning of regular, predictable, continuous activity to prohibit deconditioning, (f) recovering self-confidence and self-control by starting with a five- minute walk morning and night followed by gradual development (GET), and (g) classical CBT-procedures. A treatment manual for SCBT has been developed following [name] guidance. in use at the Division of CFS/ME, Kings College, UK (17). There will be regular supervision of the therapists in relation to this manual. All treatment sessions will be taped which will allow for quality control and satisfactory CBT guidance. Appropriate use of standard CBT will be quality assured using independent observers with CTACS quality assurance instrument afterwards (18) so that all therapists are quality assured as CBT therapists. Guidance is provided by a specialist in CBT guidance (psychiatrist, [name]) regularly once a month in a group, as well as individually when needed.

**Control group (WLC):** The control group is a waiting list control group in which the participants will be asked to wait for 16 weeks after primary assessment and randomisation before they are post-scored and then offered eight weeks of I-CBT outside the study. The ideal would have been a control period up to one year without intervention, but this will not possible due to ethical considerations.

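### Three-arm comparisons are planned at every follow-up time, but the waiting list gives an untreated control only up to its 16-week score

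*Protocol*

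**What the plan says.** In the Intervention section, the paragraph on the control group has WLC patients "wait for 16 weeks after primary assessment and randomisation before they are post-scored and then offered eight weeks of I-CBT outside the study". It then acknowledges the limit: "The ideal would have been a control period up to one year without intervention, but this will not possible due to ethical considerations".

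The Statistical analyses section states that "The three intervention cohorts will be compared at X, Y and Z months". The months are unfilled placeholders. The methods are "separate analyzes for each follow-up time (ANCOVA) as well as combined analyzes for all times (mixed random effects regression", adjusted for baseline. Nothing there restricts the times at which WLC enters a comparison. The Intention to treat section says that all patients will be accounted for, but does not mention WLC patients who start I-CBT.

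The Summary describes testing standard CBT "in a randomized, controlled 1-year follow-up trial". Hypothesis 1 is that both therapies beat WLC on SF-36 physical function; Hypothesis 2 is that the two therapies do not differ.

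**The concern.** Hypothesis 1 asks whether CBT is better than waiting. It needs a control group that has waited and has not been treated. The protocol provides one up to the 16-week score and not beyond, yet the analysis section sets out three-arm comparisons at all follow-up times without distinction.

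If WLC patients are measured after accepting I-CBT, I-CBT against WLC becomes early against delayed I-CBT, and standard CBT against WLC becomes standard CBT against a group partly treated with I-CBT. If they are not measured after week 16, the later comparisons have no observed controls, and any late WLC value from a mixed model would rest on modelling assumptions. Either way, a result labelled as CBT against waiting list at a late visit, or over all times, would not answer the main research question.

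**Working it through.** **1. Do the planned times reach past week 16?** The placeholders do not say which visits fall where. The Summary gives a 1-year follow-up, and for standard CBT "The intervention consists of 16 weekly sessions plus a booster session four weeks after the 16"th, so that arm's own treatment reaches about week 16 + 4 = 20. At least the 1-year time therefore lies after the untreated control period.

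**2. The plan's own power figure.** Inputs from the sample size paragraph: changes of 10 (I-CBT), 5 (standard CBT) and 0 (WLC), SD 15, r-squared 0.1, 40 per group, two-sided 5%.

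- Residual variance = 15² × (1 − 0.1) = 202.5.
- Three-group ANCOVA F test with 2 and 116 degrees of freedom; noncentrality = 40 × [(10−5)² + (5−5)² + (0−5)²] / 202.5 = 40 × 50 / 202.5 = 9.88. Power is 79.95%, against 80% stated.
- For changes of 10, 10 and 0: 40 × 66.67 / 202.5 = 13.17. Power is 90.4%, against 90% stated.

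Both figures reproduce. Both take the WLC change as 0, which the design supports only up to the 16-week score.

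**3. What a late contrast would estimate if WLC patients are still scored.** Two assumptions are not in the protocol: a proportion u of WLC patients takes up I-CBT, and those who do gain the planned 10 points. The late WLC mean is then 10u, and the contrast is the arm's planned change minus 10u.

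| Uptake u | I-CBT − WLC | Standard CBT − WLC, planning 10/5/0 | Standard CBT − WLC, planning 10/10/0 |
|---|---|---|---|
| 0% | +10 | +5 | +10 |
| 25% | +7.5 | +2.5 | +7.5 |
| 50% | +5 | 0 | +5 |
| 75% | +2.5 | −2.5 | +2.5 |
| 100% | 0 | −5 | 0 |

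**4. Effect on power for I-CBT against WLC.** With 40 per group, the standard error is √202.5 × √(2/40) = 14.23 × 0.2236 = 3.18. Power is Φ(contrast/3.18 − 1.96):

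- Uptake 0%: Φ(3.14 − 1.96) = 88%.
- Uptake 25%: 65%.
- Uptake 50%: Φ(1.57 − 1.96) = 35%.
- Uptake 75%: 12%.

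**5. If WLC patients are not scored after week 16.** No arithmetic applies. The late three-arm ANCOVA cannot be run, and the combined model has WLC outcome data at one time only.

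**6. What is not affected.** I-CBT against standard CBT remains a randomised comparison at every time. Confining the WLC contrast to week 16 leaves the WLC change at its planned 0, so 40 per group and the 80% and 90% power figures stand.

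**The case against.** The strongest reply is that WLC patients are scored and then treated "outside the study", which may mean that their study measurement ends at week 16. No treated controls would then enter any analysis. This stands as a limit on the claim. A reader might infer that every late control contrast is contaminated, but the protocol documents no WLC score after week 16. The supportable statement is that late contrasts are either contaminated or cannot be estimated.

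A reader might also take the Summary as promising an untreated control at one year. It does not clearly do so: the control-group paragraph says that this was not possible, and the two therapies can properly be compared at one year. The Summary needs clarifying.

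Third, one might average the contrasts over one time before and two after the crossover at full uptake, giving (10 + 0 + 0)/3 = 3.3 and (5 − 5 − 5)/3 = −1.7. The protocol gives neither that split of visits nor equal weights, nor does it say that the mixed model reports one time-averaged effect. A model with treatment-by-time terms would report each time separately. These pooled figures should not be relied on.

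Finally, the visit months may be filled in a SAP that is not at hand, and the flow chart and the outcome figures are not shown. The blank months alone are therefore not the point, nor do they show that a favourable time would be picked afterwards. What remains is that the protocol text sets three-arm comparisons at all times beside a control period that ends at 16 weeks, and does not reconcile them.

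**Conclusion.** The concern holds as an unreconciled conflict between the control-group paragraph and the Statistical analyses section. After week 16, no WLC contrast tests Hypothesis 1, whether because controls have been treated or because they are no longer measured.

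The size is illustrative. It rests on assumed uptake and on delayed patients gaining the full 10 points; the protocol gives neither. On those assumptions, half uptake halves the I-CBT contrast from 10 to 5, and full uptake removes it. For standard CBT, a reversal of sign appears above 50% uptake under the 10/5/0 values but not under 10/10/0, so it should not be presented as a general consequence. The conflict itself does not depend on these figures.

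**What to change.** Reconcile the two sections with wording to this effect:

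- The test of each therapy against WLC (Hypothesis 1) uses only the 16-week WLC score and, from each therapy arm, the already scheduled score nearest that time.
- In the mixed model, WLC contributes only baseline and week 16 to the control contrast.
- Later times, including 1 year, compare I-CBT with standard CBT only. Any later WLC data are reported separately as delayed treatment.
- The Summary says that the waiting-list-controlled effect runs to 16 weeks and that the 1-year comparison is between the two therapies.

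The change is to wording, made before analysis, and it leaves the sample size as it is. The trial would make no untreated-control claim beyond 16 weeks. It should not be assumed that all arms were scored at the same time: the protocol states a 16-week score only for WLC, and with inclusion nearly complete, scores already taken cannot be re-timed. If the therapy arms' score times differ from week 16, that difference must be stated as a limitation.
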